## Abstract

**Background:**

The prevalence of diabetes and coexisting multimorbidity rises worldwide. Treatment of this patient group can be complex. Providing an evidence-based, coherent, and patient-centred treatment of patients with multimorbidity poses a challenge in healthcare systems, which are typically designed to deliver disease-specific care. We propose an intervention comprising multidisciplinary team conferences (MDTs) to address this issue. The MDT consists of medical specialists in five different specialities meeting to discuss multimorbid diabetes patients. This protocol describes a feasibility test of MDTs designed to coordinate care and improve quality of life for people with diabetes and multimorbidity.

**Methods:**

A mixed-methods one-arm feasibility test of the MDT. Feasibility will be assessed through prospectively collected data. We will explore patient perspectives through patient-reported outcomes (PROs) and assess the feasibility of electronic questionnaires. Feasibility outcomes are recruitment, PRO completion, technical difficulties, impact of MDT, and doctor preparation time. During 17 months, up to 112 participants will be recruited. We will report results narratively and by the use of descriptive statistics. The collected data will form the basis for a future large-scale randomised trial.

**Discussion:**

A multidisciplinary approach focusing on better management of diabetic patients suffering from multimorbidity may improve functional status, quality of life, and health outcomes. Multimorbidity and diabetes are highly prevalent in our healthcare system, but we lack a solid evidence-based approach to patient-centred care for these patients. This study represents the initial steps towards building such evidence. The concept can be efficiency tested in a randomised setting, if found feasible to intervention providers and receivers. If not, we will have gained experience on how to manage diabetes and multimorbidity as well as organisational aspects, which together may generate hypotheses for research on how to handle multimorbidity in the future.

**Administrative information:**

Protocol version: 01

**Trial registration:**

NCT05913726 — registration date: 21 June 2023

**Supplementary Information:**

The online version contains supplementary material available at 10.1186/s40814-024-01517-0.

## Background

WHO defines multimorbidity as the coexistence of two or more chronic diseases in the same person [1]. Due to increasing life expectancy, an ever-increasing number of people struggle with chronic conditions and complex multimorbidity [2]. Diabetes is one of the four major groups of noncommunicable diseases as defined by the WHO, with a global prevalence in 2019 estimated to 463 million people [3]. The same year, diabetes caused two million premature deaths worldwide [4]. Diabetes is associated with several other comorbidities, such as cardiovascular diseases, mental health disorders, and cancer [5–7]. In Australia, researchers report that 90% of people with type 2 diabetes also have another chronic condition [8], and a Canadian study found that nearly 40% of people with type 2 diabetes had two or more concurrent chronic diseases [9]. A systematic review reported that one of the most frequent combinations of chronic conditions is that of cardiometabolic conditions such as high blood pressure, diabetes, obesity, and ischaemic heart disease [10]. In people with type 2 diabetes, the all-cause mortality rises with increasing number of chronic conditions [11].

Having multiple chronic conditions may often entail clinical check-ups at multiple departments and seeing many different health care providers. Coordinating treatment and collecting prescription drugs can be a challenge for these patients. A lack of coordination may confuse and mentally exhaust the patient, decrease adherence and compliance, and, ultimately, reduce life quality and expectancy [12–14]. The patient may travel like a *nomad* between departments, specialists, and across healthcare sectors, possibly left uncertain of whom to contact if problems arise.

Multidisciplinary team conferences (MDT) are utilised in many parts of the healthcare system and serve as a well-established tool to aid clinical decision-making [15–17]. MDTs promote coordination and coherence in patient care and management [18, 19]. They can tailor care and management to suit the individual patient with complex needs by bringing together expertise from different medical specialties and healthcare professionals. Historically, the MDT approach resides in oncological context where the complexity of diagnostics and treatments is high. This approach has been reported beneficial, yet researchers encourage further research in the impact of MDT on quality of life and in further strategies to incorporate patient perspectives in the MDTs [15, 19].

In recent years, the MDT approach has expanded to non-oncological fields. A recent scoping review on the topic of physician-led in-hospital MDTs in chronic non-malignant diseases concluded that MDT care for patients with multimorbidity may positively affect the treatment, but the literature is scarce [20]. Another recent review reports that MDT for people with diabetes and comorbidities has a positive effect in glycaemic control and mental health outcomes but suggests a more cross-sectorial approach in future studies [21].

Thus, Steno Diabetes Centre Odense (SDCO) has developed a concept of MDT called “Network Of doctors for Multimorbidity And Diabetes — NOMAD” which is ready to be feasibility tested before moving on to a large-scale randomised controlled trial (RCT). We have formed the following hypotheses for the feasibility test:The NOMAD intervention can function in a clinical setting and is acceptable to intervention providers and recipients.The present concept will be feasible in a future RCT.

Acceptability means that a person finds the intervention appropriate, based on anticipated or experienced cognitive and emotional responses to the intervention [22].

## Methods

### Study design

A mixed-methods one-arm feasibility study with follow-up on persons referred to the NOMAD. The study has an explorative part, looking into the content of the conference discussions and assessing mediators and moderators to feasibility of NOMAD (a process evaluation). This protocol is written in line with CONSORT 2010 statement: extension to randomised pilot and feasibility studies [23] and guidelines for inclusion of patient-reported outcomes in clinical trial protocols, SPIRIT-PRO Extension [24].

### Setting and context

The Danish population amounts to 5.8 million people [25]. Healthcare is free of charge for all citizens in Denmark. The Region of Southern Denmark, where the trial takes place, inhabits 1.2 million people [26] with Odense University Hospital (OUH) as the largest and most specialised hospital. It also serves as local hospital for approximately 275,000 people [27] (catchment area). SDCO introduced the NOMAD as a clinical initiative for all citizens who meet eligibility criteria and who live in OUH catchment area or have general practitioner (GP) on the island of Funen.

### Participants

Adult patients (over 18 years) referred to the NOMAD at OUH from August 2023 until December 2024 (17 months) who have returned written consent to participate. We did several things to ensure recruitment, such as presenting the NOMAD concept at each of the involved departments, producing a pamphlet aimed at doctors and patients, and sending a letter describing the concept as well as paying physical visits to GP. The patient is referred from clinical departments, such as Cardiology, Respiratory Medicine, Nephrology, and/or Diabetology/Steno Diabetes Centre, or from the GP. Referral criteria include patients with any type of diabetes and one or more concurrent chronic conditions within cardiology, respiratory medicine, or nephrology, and complexity in treatment/management, e.g. difficulty in specific treatment, symptoms or other patient complaints, lack of compliance, or polypharmacy.

### Intervention development

When developing the NOMAD intervention, we followed Medical Research Council’s (MRC) framework for developing and evaluating complex interventions [28] and the “Guidance on how to develop complex interventions to improve health and healthcare” [29]. The development process commenced in 2020, starting with the establishment of dedicated working and research groups. The groups consist of medical specialists within the relevant fields of medicine and researchers with expertise in relevant research areas. When establishing the NOMAD team, factors like local resources and department capacities played a role. For instance, we initially wanted a psychologist in the team, but this was not possible at the time. According to MRC guidelines, we chose a dynamic and iterative approach. An early version of the intervention was pilot-tested in 2021 resulting in a preliminary evaluation report in 2021 (available upon request) with interviews of patients and different healthcare professionals. It showed necessity for a closer collaboration with GP and the need for patient involvement in the decision-making. We refined and adjusted the intervention through working group meetings and workshops. We put great effort in understanding the possible mechanisms of change with construction of a comprehensive logic model. Figure 1 provides a simplified version of the logic model. Further, we conducted a journal audit to gain insights into topics of discussion in the NOMAD conferences. The development process resulted in a final intervention presented in Template for Intervention Description and Replication (TIDieR) format (Appendix 1) and supported by a written, generic manual in national language describing how to set up and perform this type of conferences (available upon request). We published an official local guideline for hospital staff the OUH guidelines collection. The intervention is briefly outlined below.

**Fig. 1 Fig1:**
[figure not shown]
Logic model illustrating the mechanisms of change of the NOMAD intervention. This simplified version of the original logic model focuses on elements that pertain to the feasibility study, and that we address directly or indirectly in the collected data and corresponding outcomes. The input signifies the resources needed to perform the NOMAD intervention. The red boxes indicate elements pertinent to conducting the conference and follow up. The short- and long-term results are divided into results relevant to health care professional and patients respectively. NOMAD, Network of Doctors for Multimorbidity and Diabetes; PRO, patient-reported outcome; MDT, multidisciplinary team conferences

### Intervention

Every two weeks, a senior registrar/chief physician and a resident doctor from the involved departments (cardiology, diabetes, respiratory medicine, nephrology, and clinical pharmacology) meet to discuss up to four patient cases. The patients are referred to the NOMAD by either one of the involved departments or from their GP. From time of referral to NOMAD conference, usually 1 to 4 weeks pass, allowing the diabetes department (SDCO) to make necessary preparations, such as electronically send out and receive PRO questionnaires. In addition, all participating doctors have protected time to prepare for the conference, which is defined in an agreement between the collaborating departments. Especially, the clinical pharmacologists require several hours preparation time per case to ensure a high quality and systematic review of a patient’s previous hospital contacts and medicines.

If a GP refers, he/she is encouraged to participate in the conference by video link with or without the patient.

A consultant physician from SDCO conducts the conference. The discussion proceeds in a formalised manner, ensuring all doctors get to contribute while keeping a tight schedule. One doctor forms a note of NOMAD conclusions and recommendations based on an oral discussion summary. This note also states who is responsible for following up on treatment.

Six months after the NOMAD conference, we send out the PRO questionnaire again. A healthcare professional reviews the answers and contacts the patient by telephone. This element has a twofold purpose: (1) to follow up on NOMAD recommendations and (2) to discuss their 6-month PRO-questionnaire answers.

**Fig. 2 Fig2:**
[figure not shown]
PRO questionnaires

### Progression criteria (see Table 1)

**Table 1 Tab1:** Progression criteria with traffic light system

**Progression criteria**	**Monitored how**		**Actions**	
		Green	Amber	Red
**Recruitment**	Continuously throughout the project period, simple count of inclusions every 2 weeks	3–4 patients per MDT: continue	2–3 patients per MDT: look into motivational efforts and reminder information to raise referral rates	< 2 patients per MDT: use MDT time slot to make adjustments (e.g. can nurses also refer? Allow patient self-referral?)
**Adherence to protocol**	Every 3 months, assess if there are uncertainties too great to continue (e.g. impossible to keep time schedule in MDT, technical issues like video conference not working)	All or close to all process indicators^a^ are being followed: continue	2–10 process indicators are not being followed: consider revising protocol. If time schedule in MDT is not kept, downscaling to 3 patients per MDT might be necessary	> 10 process indicators are not being followed: consider pausing the project in order to evaluate and redesign intervention
**Data completeness**	Every 6 months, evaluate if the data collection is complete enough. Missing answers in surveys? Unable to retrieve certain register data?	> 80% data completeness: continue	70–80% data completeness: make efforts to collect missing data (e.g. contacting participants)	< 70% data completeness: consider revising protocol. Can data be obtained otherwise? Can data be excluded from study?
**Participant retention**	Every 6 months, register how many participants lost to follow-up. Simple count and register reason if known (e.g. death, unwilling to participate)	Loss to follow-up caused by death, change of mind, or unable to participate will of course be accepted	If not returning questionnaire at 6-month follow-up, then contact by phone to remind and encourage	If < 75% complete follow-up, then look into protocol amendments

^a^ Process indicators are listed in Appendix 2

The number of referred patients is crucial for this study to succeed and to progress into an RCT. Our goal is four patients on each NOMAD conference. We will continuously monitor the rate of referrals in order to take action if needed. Adherence to protocol is monitored according to a list of pre-defined process indicators (Appendix 2). We also monitor data completeness and participant retention.

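### Exactly 3 patients per MDT falls in both the Green and the Amber recruitment band, and the plan does not say whether the bands apply to one conference or to an average

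*Protocol article*

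**What the plan says.** The Recruitment row of Table 1 (Progression criteria) sets three bands:

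- Green: "3–4 patients per MDT: continue".
- Amber: "2–3 patients per MDT: look into motivational efforts and reminder information to raise referral rates".
- Red: "< 2 patients per MDT: use MDT time slot to make adjustments".

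The monitoring column for this row says "Continuously throughout the project period, simple count of inclusions every 2 weeks". It names no averaging period. The text below the table states the target, "Our goal is four patients on each NOMAD conference", and the weight given to the criterion: "The number of referred patients is crucial for this study to succeed and to progress into an RCT".

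The Intervention section limits each fortnightly conference: the doctors "meet to discuss up to four patient cases". The Sample size justification section gives 28 possible conferences and a maximum of 112 patients.

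In the Adherence row of Table 1, Amber adds that if the conference timetable is not kept, "downscaling to 3 patients per MDT might be necessary".

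**The concern.** A traffic-light rule should give each possible result one colour. Here the value 3 has two: Green asks for nothing beyond carrying on, and Amber asks for corrective effort. No other sentence breaks the tie.

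The table does not show which way to resolve it. The lower recruitment edge is clean (2 is Amber, below 2 is Red). The Data completeness row is also exclusive (above 80%, 70–80%, below 70%) and places its upper boundary value in Amber. By that analogy 3 would be Amber; by the Green cell's own wording it is Green. On whole counts, the first reading leaves 4 as the only Green result, and the second makes 3 sufficient.

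At stake is a clear, pre-set reading of recruitment, which the Outcomes section lists first among the primary feasibility outcomes. The Statistical methods section plans to report these narratively, so the bands are the main fixed yardstick for this one.

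**Working it through.** **1. The plan's own figure.** 28 conferences × 4 cases = 112, as stated.

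**2. Colour of each possible count.** With a limit of four cases, the counts are 0 to 4.

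| Count | Colour |
|---|---|
| 0, 1 | Red |
| 2 | Amber |
| 3 | Green and Amber |
| 4 | Green |

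One of five values has two colours.

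**3. How often this arises if each conference is scored.** The protocol gives no expected fill rate, so p below is an assumption, as is independent filling of the four slots. The formula is P(count = 3) = 4 × p³ × (1 − p). At p = 0.75, for example, 4 × 0.4219 × 0.25 = 0.422.

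| Assumed fill rate p | Mean per MDT | P(exactly 3) | Expected conferences of 28 |
|---|---|---|---|
| 0.50 | 2.0 | 0.250 | 7.0 |
| 0.60 | 2.4 | 0.346 | 9.7 |
| 0.70 | 2.8 | 0.412 | 11.5 |
| 0.75 | 3.0 | 0.422 | 11.8 |
| 0.80 | 3.2 | 0.410 | 11.5 |
| 0.85 | 3.4 | 0.368 | 10.3 |
| 0.90 | 3.6 | 0.292 | 8.2 |
| 0.95 | 3.8 | 0.171 | 4.8 |

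For fill rates of 60–80% the share is about 35–42%. It is still 37% at 85%, and falls to 25% at 50% and 17% at 95%.

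**4. How often this arises if the whole-study mean is scored.** The mean is exactly 3.0 only when the total is 28 × 3 = 84, which is 84/112 = 75% of slots. Under the same model, P(total = 84) = C(112, 84) × p⁸⁴ × (1 − p)²⁸. This is 0.044 at p = 0.70, 0.087 at p = 0.75, 0.038 at p = 0.80, and below 0.01 at p ≤ 0.65 or p ≥ 0.85. The maximum is therefore about 9%.

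**5. If capacity is cut to 3.** A completely full conference then sits in the overlap. If 3 is read as Amber, Green cannot be reached. If 3 is read as Green, a Green mean requires every slot to be filled.

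**The case against.** The strongest reply is that this is a small boundary slip with little consequence. Several parts of that reply stand.

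- **The two colours do not give opposite instructions.** A reader might infer that they do. Amber does not pause or stop anything, and the team could continue and send reminders at the same time. Outreach to departments and GPs is already part of the study (Participants section).
- **The documents do not make 3 the most likely count.** They give no expected rate, and the only target is four. In the model above, 3 is the single most likely count only for fill rates between 60% and 80%.
- **The row is not a go/no-go rule for the RCT.** Its actions are operational, and even Red only prompts changes to referral routes. Table 1 does not rank its four criteria, so calling this the main one is an inference from the word crucial.
- **A run of false Reds from single thin conferences is not established.** The table does not say that each fortnightly count is scored alone. Modelling referrals as Poisson with mean 3 does not show it either: that puts 18.5% of the distribution on 5 or more, above the limit of four. If the excess is lost, the mean is 2.68, which is already Amber.
- **The downscaling case is conditional.** It arises only if the timetable is not kept.

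The reply does not remove the overlap. It also does not settle the unit of scoring: patients per MDT and the rate of referrals suggest an average, whereas a fortnightly count matched to a fortnightly conference suggests single meetings.

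**Conclusion.** The Recruitment row is wrong as written: a value of exactly 3 is both Green and Amber, with no rule to choose between them. This follows from the text alone and needs no model.

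The practical size does depend on assumptions. If single conferences are scored, the overlap could affect about 10 to 12 of 28 conferences at fill rates of 60–80%, assuming independent slots. If the whole-study mean is scored, it matters only at a total of exactly 84, with probability of about 9% or less. The protocol does not say which applies.

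A reader might go further and infer that the verdict on progressing to an RCT is left open to choice after the data are seen. The documents support this only at the value 3: all other values have one colour, and no hypothesis test depends on the boundary. Severity is minor to moderate.

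**What to change.** Edit the Recruitment row of Table 1 and add a sentence or two beneath it.

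1. Make the bands exclusive, for example Green ≥3, Amber ≥2 and <3, Red <2. With 28 conferences held, a total of 84 (mean 3.0) is then Green, 83 (2.96) is Amber, 56 (2.0) is Amber and 55 (1.96) is Red.
2. State that the progression verdict is scored on the mean number of patients per MDT held, and that the two-weekly counts serve operational monitoring.
3. State in advance how the bands apply if capacity is reduced to 3 per MDT. Converting the cut-points to a share of slots is not a neutral solution: 75% of 3 is 2.25 patients per MDT, a level that the current table places in Amber. Whichever rule is chosen should be written down before the reduction takes effect.

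The cost is one table edit and a line or two of text. No new data are needed. A particular running-average window is not required to cure the defect.

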### Process evaluation

In order to gain further understanding of intervention mechanisms, organisation, and acceptability among end users, we consider a qualitative process evaluation appropriate. By conducting semi-structured interviews with intervention providers, we hope to enlighten mediators and moderators to successful intervention organisation. When selecting individuals for interviews, we will keep a principle of diversity in mind, making sure the interviewees represent both genders, experience levels, medical specialties, and roles in relation to the current project. Interviews will be transcribed verbatim, and we will use a thematic analysis approach to organise and condensate the information [41]. The results from the qualitative process evaluation will be published in a separate paper.

### Variables

We divide variables into two categories: process-related variables and person-related variables. The process-related variables we subdivide according to chronology: before, during, and after the NOMAD conference. Examples of process-related variables are reason for referral, who is referring and does the MDT keep time schedule. We subdivide the person-related variables into clinical (e.g. blood pressure, HbA1C, creatinine), PROs, and organisational variables (number of hospital contacts, where diabetes is treated, number of active treatment courses, physician learning). A full list of variables is provided in Appendix 3 (Figure 3b).

### Outcomes

Primary outcomes will enlighten feasibility. These include recruitment, proportion of completed PRO-questionnaires, amount of technical difficulties in relation to the conference, count of how often discussions exceed 30 min, and how many minutes the clinicians take to prepare for MDT. Secondary outcomes will elucidate possible effects of the NOMAD intervention and include clinical effects for the patient and degrees of clinician self-reported learning.

